### **7.3.4. Vital Signs**

Supine and standing blood pressure, supine and standing pulse rate, and oral body temperature will be assessed at the times indicated in the Schedule of Assessments in [Appendix 5](#). Vital signs may also be performed at other times if judged to be clinically appropriate or if the ongoing review of the data suggests a more detailed assessment of vital signs is required.

Blood pressure and pulse rate will be measured in triplicate at approximately 2-minute intervals at Day 1 predose for Parts A through C and Day 1 prior to the first dose in Part D. The median value will be used as the baseline value in the data analysis. All subsequent

measurements will be performed singly and repeated once if outside the relevant clinical reference ranges. Oral body temperature will be measured singly.

Subjects must be supine for at least 5 minutes before blood pressure and pulse rate measurements.

For orthostatic vital signs measurements, the supine blood pressure and pulse rate will be measured after the subject has been supine for at least 5 minutes. The subject will then stand for at least 2 minutes and the standing blood pressure and pulse rate will be measured.

### **7.3.5. Electrocardiogram**

#### **7.3.5.1. Safety 12-Lead Electrocardiogram**

Resting 12-lead ECGs will be recorded after the subject has been supine and at rest for at least 5 minutes at the times indicated in the Schedule of Assessments in [Appendix 5](#). In Parts A and B, these safety ECGs can be obtained from the digital recorder used for continuous ECG monitoring or from a separate ECG machine. Twelve-lead ECGs will be repeated if either of the following criteria apply:

- QTcF value >500 msec
- QTcF change from the baseline (Day -1) is >60 msec.

Additional 12-lead ECGs may be performed at other times if judged to be clinically appropriate or if the ongoing review of the data suggests a more detailed assessment of ECGs is required. The Investigator (or designee) will perform a clinical assessment of each 12-lead ECG.

For Parts A, B, and D, Day -1 baseline 12-lead ECGs will be measured in triplicate at approximately 2-minute intervals. The mean value will be used as the baseline value in the data analysis. All subsequent measurements will be performed singly and repeated once if outside the relevant clinical reference ranges. For Part C, all ECG measurements will be performed in triplicate at approximately 3- to 5-minute intervals and repeats will be performed in triplicate if outside the relevant clinical reference ranges.

#### **7.3.5.2. Continuous 12-lead Electrocardiogram Monitoring**

Continuous 12-lead ECG monitoring using a Mortara Surveyor system will be performed in Parts A and B only at the times indicated in the Schedule of Assessments in [Appendix 5](#). If necessary, the predose timepoints can occur up to 20 minutes prior to the indicated time.

Subjects will be supine for at least 5 minutes before the extraction timepoint and for 5 minutes from the start of each extraction timepoint (each extraction will last for 5 minutes). Environmental distractions (eg, television, radio, conversation) should be avoided during the pre-ECG resting period and during ECG recording.

When coinciding, vital signs assessments and PK sampling should always be performed after the ECG extraction time window. If a separate ECG machine is being used for safety assessments described in [Section 7.3.5.1](#), that machine should be in place prior to the

extraction window to permit safety ECGs to be recorded irrespective of the extraction window. If the machine is not in place prior to the extraction window, safety ECGs must be recorded after the extraction window. If an integral system is used, safety ECGs may be recorded irrespective of the extraction window.

All continuous ECG data collected on study will be archived without extraction or analysis. If the decision is made to extract and analyse the continuous ECG data, the following will be the procedure at the central ECG laboratory (ERT, Rochester, New York, USA), and the analysis will not be reported in the scope of this study:

The continuous 12-lead digital ECG data will be stored prior to uploading to ERT. The ECGs to be used in the analyses will be selected by pre-determined timepoints as defined in the Schedule of Assessments in [Appendix 5](#) and will be read centrally by ERT.

The following principals will be followed in ERT's core laboratory:

- ECG analysts are blinded to the subject, visit, and treatment allocation.
- Baseline and on-treatment ECGs for a particular subject will be over-read on the same lead and will be analysed by the same reader.
- The primary analysis lead is lead II. If lead II is not analysable, then the primary lead of analysis will be changed to another lead for the entire subject data set.

The following is a brief description of ECG analysis methods utilised by ERT's core laboratory.

#### **7.3.5.3. TQT Plus ECG Extraction Technique**

Ten 14-second digital 12-lead ECG tracings will be extracted from the continuous Holter recordings using the 'TQT Plus method,' a computer-assisted and statistical process utilised by ERT. The method enables extraction of ECGs with the lowest HR variability and noise within the protocol-specified extraction time window (eg, the HR and QT changes from beat-to-beat in the range of <10%). At each protocol-specified timepoint, 10 ECG replicates will be extracted from a 5-minute "ECG window" (typically, the last 5 minutes of the 15-minute period when the subject is maintained in a supine or semi-recumbent quiet position).

#### **7.3.5.4. Expert-precision QT Analysis**

Expert-precision QT analysis will be performed on all analysable (nonartifact) beats in the 10 ECG replicates. Statistical quality control procedures will be used to review and assess all beats and identify "high" and "low" confidence beats using several criteria, including:

- QT or QTc values exceeding or below certain thresholds (biologically unlikely)
- RR values exceeding or below certain thresholds (biologically unlikely)
- rapid changes in QT, QTc, or RR from beat to beat.

Measurements of all primary ECG parameters (QT, QTc, RR) in all recorded beats of all replicates that are deemed "high confidence" will be performed using COMPAS software.

All low confidence beats will be reviewed manually and adjudicated using pass-fail criteria. The final quality control assessment will be performed by a cardiologist. The beats found acceptable by manual review will be included in the analysis. The median QT, QTc, and RR value from each extracted replicate will be calculated, and then the mean of all available medians from a nominal timepoint will be used as the subject's reportable value at that timepoint.

Categorical T-wave morphology analysis (Table 6) and the measurement of PR and QRS intervals will be performed manually in 3 of the 10 ECG replicates at each timepoint. Each fiducial point (onset of P wave, onset of Q wave, offset of S wave, and offset of T wave) will be electronically marked.

**Table 6: T-wave Morphology Categories (Assessed Manually)**

| Category           | Description                                                                                                                                                       |
|--------------------|-------------------------------------------------------------------------------------------------------------------------------------------------------------------|
| Normal T wave      | Any T wave not meeting any criterion below                                                                                                                        |
| Flat T waves       | T-wave amplitude <1 mm (either positive or negative) including flat isoelectric line                                                                              |
| Notched T wave (+) | Presence of notch(es) of at least 0.05 mV amplitude on ascending or descending arm of the positive T wave                                                         |
| Biphasic           | T wave that contains a second component with an opposite phase that is at least 0.1 mV deep (both positive and negative/positive and polyphasic T waves included) |
| Normal T wave (-)  | T-wave amplitude that is negative, without biphasic T wave or notches                                                                                             |
| Notched T wave (-) | Presence of notch(es) of at least 0.05 mV amplitude on descending or ascending arm of the negative T wave                                                         |

In addition to the T-wave categorical analysis, the presence of abnormal U waves will be noted.

### 7.3.6. Physical Examination

A complete physical examination or symptom-directed physical examination will be performed at the timepoints specified in the Schedule of Assessments in [Appendix 5](#). The complete physical examination will include the following systems: general appearance; skin; lymph nodes; head, ears, eyes, nose, and throat; neck; thorax/lungs; cardiovascular; abdomen; musculoskeletal; and neurological.

### 7.3.7. Body Weight

Body weight (in underclothes) will be recorded at the times indicated in the Schedule of Assessments in [Appendix 5](#).

### 7.3.8. Genotyping

A 3-mL blood sample for genotyping will be collected at Check-in. Analysis of NQO1 may be performed. Any remaining genotyping sample will be stored in case additional genotyping of uridine 5'-diphospho-glucuronosyltransferase or CYP enzymes would aid in the interpretation of the study results.

### **7.3.9. Exit Interview**

An exit interview will be conducted with all patients in Part C on Day 11. Patients will be asked their perspective on their experiences during study participation.

## **8. SAMPLE SIZE AND STATISTICAL DATA ANALYSIS**

A Statistical Analysis Plan (SAP) describing the handling of data issues and the planned statistical analyses in more detail will be prepared by Covance's Biostatistics Department before database release.

### **8.1. Determination of Sample Size**

No formal statistical assessment, in terms of sample size, has been conducted. However, the number of subjects in each part of the present study is common in early clinical pharmacology studies and is considered sufficient to achieve the objectives of the study.

### **8.2. Analysis Populations**

#### **8.2.1. Pharmacokinetic Population**

The PK population will include all subjects who received at least 1 dose of KL1333 and have evaluable PK data. A subject may be excluded from the PK summary statistics and statistical analysis if the subject has an AE of vomiting that occurs at or before 2 times median  $T_{max}$ .

#### **8.2.2. Pharmacodynamic Population**

The PD population will include all subjects who received at least 1 dose of study treatment (KL1333 or placebo) and for whom PD markers can be evaluated.

#### **8.2.3. Safety Population**

The safety population will include all subjects who received at least 1 dose of study treatment (KL1333 or placebo) and have at least 1 postdose safety assessment.

#### **8.2.4. QT/QTc Population**

The QT/QTc population will include all subjects in the safety population who had measurements at baseline as well as on treatment, with at least 1 postdose timepoint with a valid  $\Delta QTcF$  value. This analysis population will be used for the by-timepoint and categorical analyses for the cardiodynamic ECG parameters.

#### **8.2.5. PK/QTc Population**

The PK/QTc population will include all subjects who are in both the QT/QTc and PK populations with at least 1 pair of postdose PK and QTcF data from the same timepoint. This analysis population will be used for the concentration-QTc analysis.

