## **7.1. Pharmacokinetic Assessments**

### **7.1.1. Sample Collection and Processing**

Blood samples (approximately  $1 \times 3$  mL) will be collected by venepuncture or cannulation at the times indicated in the Schedule of Assessments in [Appendix 5](#). Furthermore, up to 3 additional blood samples may be taken from each subject per treatment period. Any changes to the scheduled times of PK assessments will be agreed with the Sponsor and documented in the Trial Master File (TMF). Samples taken from subjects who received placebo will not be analysed.

Procedures for collection, processing, and shipping of PK blood samples will be detailed in a separate document.

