#### **8.5.1.3. Concentration-QTc Analysis (Primary Analysis)**

The relationship between KL1333 plasma concentration and  $\Delta$ QTcF will be quantified using a linear mixed-effects modelling approach with  $\Delta$ QTcF as a dependent variable, drug plasma

concentration as a continuous covariate (ie, 0 for placebo), centred baseline QTcF (ie, baseline QTcF for individual subject at each postbaseline timepoint subtracting the population mean baseline QTcF for all subjects) as an additional covariate, study treatment (active = 1 or placebo = 0) and time (ie, all postbaseline timepoints on Days 1, 2, and 10) as categorical factors, and a random intercept and slope per subject. The degree of freedom estimates will be determined by the Kenward-Roger method. From the model, the slope (ie, the regression parameter for the concentration) and the treatment effect-specific intercept (defined as the difference between active and placebo) will be estimated together with 2-sided 90% CIs. The estimates for the time effects will be reported with degrees of freedom and SE.

The geometric mean of the individual  $C_{\max}$  values for subjects at each dose of active drug will be determined. The predicted effect and its 2-sided 90% CI for  $\Delta\Delta\text{QTcF}$  (ie, slope estimate + treatment effect-specific intercept) at this geometric mean  $C_{\max}$  will be obtained. If the upper bound of the 2-sided 90% CI of the model-predicted QTcF effect is below 10 msec at clinically relevant plasma levels of KL1333, it will be concluded that KL1333 does not cause clinically-concerning QTc prolongation.

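### The PK/QTc population as defined excludes every placebo subject, but the concentration-QTc model assigned to it needs placebo records to estimate its placebo-corrected effect

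*Protocol*

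**What the plan says.** **Population.** Protocol Section 8.2.5 reads: "The PK/QTc population will include all subjects who are in both the QT/QTc and PK populations with at least 1 pair of postdose PK and" a time-matched QTcF value. The same section adds: "This analysis population will be used for the concentration-QTc analysis". One of its two parent populations is defined in Section 8.2.1: "The PK population will include all subjects who received at least 1 dose of KL1333 and have evaluable PK data". On plasma samples, Section 7.1.1 says: "Samples taken from subjects who received placebo will not be analysed".

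**Model.** Section 8.5.1.3 specifies a linear mixed-effects model for change from baseline in QTcF. Its terms include "concentration as a continuous covariate (ie, 0 for placebo), centred baseline QTcF" as a further covariate, and "study treatment (active = 1 or placebo = 0) and time (ie, all postbaseline timepoints on Days 1, 2, and 10) as categorical factors". The section defines the treatment-specific intercept as active minus placebo. It predicts the placebo-corrected effect at the geometric mean Cmax of each dose, and concludes there is no concerning prolongation if the upper 2-sided 90% limit is below 10 msec. It then adjusts observed values for the plot by a time effect described as the diurnal effect under placebo. Section 8.5.1.3.1 treats a significant intercept as a possible sign of hysteresis.

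**Status.** Section 8.5.1 calls this the primary analysis of the cardiodynamic ECG evaluation in Parts A and B. Section 2.1 lists the ECG objective as exploratory. Section 7.3.5.2 says continuous ECG data are archived, and that any later extraction and analysis is reported outside this study.

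**The concern.** The population definition and the model contradict each other. The definition admits only KL1333 recipients. The model relies on placebo records for its treatment factor, its intercept, its time effects and its decision quantity. This is a rule the protocol states wrongly, so it is not a detail left to the SAP, and an SAP could correct it only by departing from the protocol.

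If the analysis is run later, the text in Sections 8.2.5 and 8.5.1.3 is its prespecification. An analyst who applies the population flag deletes the comparator. One who ignores the flag deviates from the protocol. Section 3.4 says the continuous ECGs are collected with a possible thorough QT waiver in view, and a population correction made after unblinding would be harder to defend in that setting.

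**Working it through.** The protocol gives no sample-size or power figure for this analysis (Section 8.1), so there is no stated number to reproduce. The check is set logic followed by estimability.

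**1. Who enters the PK/QTc population**

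| Condition | KL1333 subject | Placebo subject |
|---|---|---|
| In QT/QTc population (8.2.4) | can be met | can be met |
| At least one dose of KL1333 (8.2.1) | met | never met |
| Measured postdose PK value to pair with QTcF (8.2.5, 7.1.1) | can be met | never met |

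The zero-substitution rule in Section 8.5.1.1 covers concentrations below the assay limit. It does not admit a subject who received no KL1333 and whose samples are not assayed. The omission of placebo from 8.2.1 also stands out because Sections 8.2.2 and 8.2.3 name both KL1333 and placebo.

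**2. How many are lost**

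Allocation is 6 active to 2 placebo per cohort, so 2/8 = 25% in each.
- Groups A1, B1 and B2: 3 x 2 = 6 of 3 x 8 = 24.
- Maximum in Parts A and B, with 3 + 5 = 8 cohorts: 8 x 2 = 16 of 8 x 8 = 64.
- Placebo subjects admitted as written: 0 of 6 and 0 of 16.

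**3. What can be estimated**

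Write the fixed part as

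change in QTcF = time_j + d x treatment + b x concentration + g x centred baseline.

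With T timepoints there are T + 3 columns: T time indicators, treatment, concentration and baseline.
- *With placebo at concentration 0:* rank T + 3, and all terms are estimable.
- *Active subjects only:* treatment equals 1 on every record, so its column is the sum of the T time indicators and the rank is T + 2.

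A numerical check used T = 22 (11 postdose extractions on each of Part B Days 1 and 10) with simulated concentrations. It gave the same result for 18 active and 6 placebo as for 48 active and 16 placebo:

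| Quantity | Placebo in | Placebo out |
|---|---|---|
| Rank of 25 columns | 25 | 24 |
| Intercept d | estimable | not estimable |
| Slope b | estimable | estimable |
| b x C + d (illustrative C = 300) | estimable | not estimable |

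T = 22 is not quite the protocol's set. Baseline is the Day 1 predose mean (8.5.1.2), so the three Day 10 predose extractions in the Part B schedule are postbaseline, and the last 24-hour extraction falls on Day 11. Counting Days 1, 2 and 10 gives 11 + 3 + 10 = 24 timepoints, or 25 with Day 11. The columns become 27 or 28 and the active-only rank 26 or 27. The shortfall is one whatever T is.

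**4. What a literal run returns**

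Only (time_j + d) and b are identified. Section 8.5.1.3 writes the prediction as slope estimate plus intercept at the geometric mean Cmax. Read as b x Cmax + d, it has no estimate and no 90% CI. If the software sets the aliased term to zero, the output is b x Cmax, which differs from the target by d. The time-adjusted values for the plot would also have d subtracted, because the time effects then come from subjects on drug.

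**The case against.** - **The intent is plain.** Section 8.5.1.3 says placebo concentration is 0 and codes placebo in the treatment factor, so an analyst would probably keep placebo in. This stands as evidence of intent and explains why the repair is small. It does not remove the contradiction, because 8.2.5 expressly assigns the population.
- **The analysis may never be run here.** This stands. The objective and endpoints are exploratory (2.1, 2.2.3), and Section 7.3.5.2 makes the analysis conditional and places it outside this study's report. A reader might infer from the label primary that a main trial endpoint fails. The documents do not support that. The primary endpoints in 2.2.1 are adverse events, laboratory tests, 12-lead ECG parameters, vital signs and physical examinations. The QTcF stopping criterion in 3.7 uses observed values.
- **Placebo-corrected QTcF is still examined.** This stands. The by-timepoint analysis (8.5.1.4) uses the QT/QTc population with pooled placebo and gives 90% CIs at each timepoint. Section 8.5.1.3.1 bases its hysteresis plots and trigger on placebo-corrected by-timepoint results. A reader might infer that every check for a delayed or concentration-independent effect is lost. Only the model intercept as a diagnostic is lost.
- **No bias has been sized.** This stands. A reader might infer a biased QTc conclusion, but the protocol gives no value for d, and 8.5.1.3.1 calls a significant intercept biologically implausible. If d is zero, b x Cmax equals the target.

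**Conclusion.** The point holds as an internal contradiction. Taken literally, Sections 8.2.1, 8.2.5 and 7.1.1 remove all placebo subjects (25% of each cohort) from the concentration-QTc model. The intercept and the placebo-corrected prediction compared with 10 msec then cannot be estimated. This needs no assumption about QTcF variability, effect size or concentrations. It rests on the literal population text and on the model having categorical time and a treatment factor.

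The reach is narrow: one exploratory, conditional cardiodynamic analysis reported outside this study. The concentration slope, the by-timepoint analysis, the primary safety endpoints and the dose-escalation stopping rules are unaffected. No numerical bias can be stated. The definition should be corrected before any concentration-QTc analysis is run.

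**What to change.** Reword Section 8.2.5 so that the PK/QTc population comprises all QT/QTc-population subjects who either:

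- received KL1333, are in the PK population, and have at least one postdose PK/QTcF pair from the same timepoint; or
- received placebo and have at least one valid postdose change-from-baseline QTcF value, with concentration set to 0.

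The PK population in 8.2.1 can stay as it is, since it serves the PK summaries. The rewording restores full rank, so the intercept, the slope and the placebo-corrected prediction all become estimable.

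The cost is one sentence in the protocol, carried into the SAP. No new data, samples or visits are needed, because continuous ECGs are already scheduled for Parts A and B without distinction by treatment. The change should be documented before any concentration-QTc analysis, and preferably before any unblinded ECG data are seen.

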### **8.3. Pharmacokinetic Analyses**

Noncompartmental PK analysis will be performed on individual plasma concentration data, using commercial software such as Phoenix WinNonlin®. Plasma concentrations of KL1333 and PK parameters will be listed and summarised using descriptive statistics. Individual and mean KL1333 concentration-time profiles will also be presented graphically.

In Part A, where data are available, the effect of food on KL1333 will be investigated using an analysis of variance (ANOVA) model as appropriate. In Part B, where data are available, KL1333 dose proportionality will be examined across the dose cohorts. The PK parameters will be analysed for dose proportionality using a power model approach or ANOVA model as appropriate.

### **8.4. Pharmacodynamic Analyses**

Pharmacodynamic parameters will be listed and summarised using descriptive statistics. Formal statistical analysis of PD data in Parts C and D is planned and will be described in more detail in the SAP.

